## Results

This study was registered to ClinicalTrials.gov (NCT05320224) in March 2022. Recruitment and data collection began in March 2022.

## Discussion

### Methodological Strengths

One strength of this study is the evaluation of the intervention acceptability from multiple sources: ICU patients, families, and nursing staff. This will allow us to gain access to the different perspectives of the various stakeholders and acquire a more comprehensive understanding of the overall acceptability of the intervention. The crossover design is another strength as it allows each patient participant to be their own control, thus reducing confounding factors that are usually present in between-subject designs [50,51]. Moreover, the crossover design will allow for patient participants able to self-report to share their preference between the POMI and the CTL because they will experience both interventions. Information about participant preference will add rich qualitative data beyond the quantitative comparison of preliminary efficacy [41,51]. The crossover design is relevant to use during procedures that are planned within a short period of time (eg, molar extractions at 2 different times) [50]. In addition to intervention comparisons and patient participant preferences, we will be able to determine the pain and distress differences individually (numerically) and compute the proportion of patient participants for whom the treatment was effective in reducing pain by more than 1 point on a 0-10 NRS, for example [51]. The crossover design will also enable us to describe whether any reduction in pain or distress was qualified as meaningful by the patient participant (for those able to self-report). These data could later contribute to the understanding of the minimally clinically significant difference in procedural pain in the adult ICU population [51]. Knowing that patient participants will receive both interventions as part of the crossover design may allow them to think more objectively about pain levels in each intervention period (thus minimizing the placebo effect) compared to if they participated in a parallel-group trial, in which the patient participants’ hope to receive the intervention may influence their pain rating [50]. Finally, blinding patient participants unable to self-report will reduce the risk of bias based on these participants’ expectations of music efficacy to reduce pain.

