**Methods:**

A single-blind 2×2 crossover pilot RCT will be conducted. Patients will undergo 1 sequence of 2 interventions: the POMI which delivers music based on patients’ preferences via headphones or music pillow for 20-30 minutes and the control intervention (headphones or pillow without music). The sequence of the interventions will be inverted with a 4-hour washout period. Timing of the interventions will be before a planned bed turning procedure. Each patient will undergo 1 session of music. Twenty-four patients will be recruited. Patients able to self-report (n=12), family members of patients unable to self-report (n=12), and nursing staff (n=12) involved in the bed turning procedure will be invited to complete a short questionnaire on the POMI acceptability. Data will be collected on the feasibility of the intervention delivery (ie, time spent creating a playlist, any issue related to headphones/pillow or music delivery, environmental noises, and intervention interruptions) and research methods (ie, number of patients screened, recruited, randomized, and included in the analysis). Pain scores will be obtained before and after intervention delivery.

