## Methods

### Design

A single-blind 2×2 crossover pilot RCT is being conducted to evaluate the acceptability, feasibility, and preliminary efficacy of the POMI. Recruitment is planned to occur over a period of 6 months during which we aim to enroll a total of 24 patient participants. As shown in Figure 1, each participating patient is randomly assigned to 1 sequence (sequence 1 or 2) of 2 intervention periods: the POMI and the CTL (headphones or pillow without music). Patients in sequence 1 receive the POMI during the first intervention period, followed by the CTL in the second intervention period; and patients in sequence 2 receive the CTL first, followed by the POMI. Each 20-30–minute intervention period is provided before a bed turning procedure that is planned as part of the participating patient’s usual care by the nursing staff. There is a 4-hour minimum washout period between both intervention periods, with data collected during the day and evening. Data collection begins as soon as possible following recruitment, always in coordination with patient care. Therefore, the first period of data collection may occur in the daytime or in the evening.

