#### Preliminary Efficacy of POMI on Acute Pain

Pain will be assessed at 4 different timepoints for each intervention period: before the intervention, immediately after the intervention, during the bed turning procedure, and 30 minutes after the bed turning procedure (Figure 1, T_0_-T_3_). Pain assessments will be performed using validated tools as recommended in ICU clinical practice guidelines [1]. For all patient participants, the CPOT will be used because it is one of the most valid behavioral scales for assessing pain in critically ill adults [42]. In addition to the CPOT, patient participants able to self-report will be asked to rate their pain intensity using the 0-10 Faces Pain Thermometer [43] and their pain distress on a 0-10 NRS [44,45].

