### Methodological Limitations and Mitigation Strategies

The Initiative on Methods, Measurement, and Pain Assessment in Clinical Trials recommendations state that the use of a crossover trial at an earlier stage study, followed by confirmation of the results in a larger parallel-group study, is an efficient approach, as long as a washout period is carefully planned to minimize or avoid carryover effects [50]. To allow for any pain-reducing effect of the POMI to dissipate before the CTL, there will be a washout period of at least 4 hours between both intervention periods, based on previous data on the duration of the analgesic effect of music on pain [32]. Due to the sample size and to evaluate the time effect, the Friedman and Wilcoxon rank sum tests will be used when analyzing pain-related data for each subgroup [51]. To avoid response shifts due to the crossover design, baseline pain intensity will be measured for each intervention period (T_0_ in Figure 1). Because blinding will be difficult with patient participants receiving both the POMI and the CTL, there is a risk of ascertainment bias for patient participants. To address this, patient participants able to self-report will be asked about their perception of how effective they think the music is compared to the CTL. To minimize possible interruptions and noise during intervention periods, the nurse responsible for the patient will be met to discuss and plan for the best time to start the intervention period, prior to a scheduled bed turn.

Due to the current context of the pandemic and this study being conducted in an ICU setting, it is possible that limited family visits and nursing staff shortages will impact recruitment from these populations. To mitigate these possible limitations, meeting families at the bedside will be coordinated with the nursing staff.

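### An unreplicated 2×2 crossover cannot show in what proportion of patients the music worked; the more-than-1-point count needs neutral wording, a mirror count and the right scale name

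*Protocol article*

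**What the plan says.** In the protocol article's Discussion, under Methodological Strengths, the crossover is credited with giving numerical individual differences in pain and distress. It is also said to allow the team to "compute the proportion of patient participants for whom the treatment was effective in reducing pain by more than 1 point on a 0-10 NRS". The sentence closes by marking this as an example.

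The design is described elsewhere in the article:

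- Methods, Design: "each participating patient is randomly assigned to 1 sequence (sequence 1 or 2) of 2 intervention periods", one with music (POMI) and one control (CTL).
- Abstract, Methods: "Each patient will undergo 1 session of music".
- Outcomes, Preliminary Efficacy of POMI on Acute Pain: "Pain will be assessed at 4 different timepoints for each intervention period" (T0 to T3). Patients able to self-report also "rate their pain intensity using the 0-10 Faces Pain Thermometer [43] and their pain distress on a 0-10 NRS".
- Methodological Limitations and Mitigation Strategies: "baseline pain intensity will be measured for each intervention period".

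The more-than-1-point proportion appears neither among the Outcomes nor in the Preliminary Efficacy part of the Data Analysis. The latter states that efficacy findings will not inform the decision on a full-scale trial.

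**The concern.** The Discussion names a quantity about individuals, the share of patients in whom the treatment worked, and presents it as something this design delivers. A crossover does estimate an average within-patient contrast. Separating a patient's own response from that patient's ordinary variation needs each condition to be repeated in the same patient, and here neither is.

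A count of patients past a one-sided cut also has no natural zero. Some patients score lower in the music period by chance, and a count described as effectiveness would credit those patients to the music. What is at stake is how the result is read and carried forward, not the trial's conduct or its decision rules.

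A second, simpler problem is that the sentence measures pain reduction on an NRS, which the Outcomes section does not use for pain intensity.

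**Working it through.** **Denominator.** The only computed figure in the article is the recruited number per group. Ten participants inflated for 15% attrition is 10/(1 − 0.15) = 11.76, rounded up to 12, which matches the stated 12. Self-report scores therefore come from 12 recruited patients, about 10 after attrition. The article gives no SD, within-patient correlation or expected responder proportion, so those below are assumptions.

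**Identification.** For patient i at one time point, let D = CTL score − POMI score = τ ± π + ε. Here τ is the patient's own effect, π the period effect (its sign set by sequence) and ε ordinary variation between the two periods. There is one D per patient at each time point. T0 to T3 do not replicate the condition, because they are taken in different circumstances: before, just after, during turning and 30 minutes later. The two baselines say something about variation between periods but do not fix τ for a patient.

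Take π = 0 and D normal with mean 0 and SD 2. The observed share above 1 is 1 − Φ(1/2) = 31%. The true share with τ > 1 could be:

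- 0%, if nobody has an effect and all variation is noise;
- 1 − Φ(1/√2) = 24%, if half the variance is variation in τ;
- 31%, if there is no noise.

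The error can also go the other way. If every patient gains exactly 2 points (true share 100%) and the noise SD is 2, the observed share is 1 − Φ((1 − 2)/2) = 69%.

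**Share passing the cut with no effect.** SD_D = SD × √(2(1 − ρ)); for example, SD 2 and ρ 0.5 give SD_D = 2. For a continuous score the share is 1 − Φ(1/SD_D). With whole-number scores, more than 1 means at least 2, which is about 1 − Φ(1.5/SD_D).

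| SD_D (assumed) | Continuous | Whole-number |
|---|---|---|
| 1.0 | 16% | 7% |
| 1.5 | 25% | 16% |
| 2.0 | 31% | 23% |
| 2.5 | 34% | 27% |
| 3.0 | 37% | 31% |

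Whole-number scores bounded at 0 to 10 were also simulated (400,000 draws per scenario; mean 4 to 5, SD 1.5 to 2.5, ρ 0.3 to 0.8):

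- contrast at one time point: about 6% to 30%;
- difference between periods in change from baseline (four equally correlated scores): about 15% to 36%.

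Together these give about 6% to 36%. The continuous formula over the same SDs and correlations runs from 15% to 37%, so the upper end is essentially the same.

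**In patients.** Of 12, 6% to 36% is 0.7 to 4.3 patients. At a chance rate of 25%, 3 or more of 12 pass with probability 0.61 and 4 or more with probability 0.35. An observed 3/12 has an exact 95% CI of 5% to 57%.

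**Scale.** The Outcomes section assigns intensity to the 0-10 Faces Pain Thermometer and distress to the 0-10 NRS. The Discussion sentence speaks of reducing pain on a 0-10 NRS. No assumption is needed to see the mismatch.

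**The case against.** The strongest reply is that this is one illustrative sentence in a Discussion. It is not an endpoint, no threshold or decision depends on it, and the Data Analysis section reserves any formal efficacy hypothesis for a full-scale trial. That stands and sets the severity. It does not make the sentence right, because the article asserts a property that the design lacks. An article may leave the exact time point and contrast to a fuller document, so their absence is not counted here as an error.

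Several stronger readings are tempting, but the article does not support them:

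- **Only one score per condition.** There are four per period, including a baseline. What is single is the period.
- **A fixed quarter to a third would qualify by chance.** That needs a continuous score and SD_D of about 1.5 to 2.3. With whole-number scores it needs about 2.2 to 3.5. The article gives no SD.
- **The count can never be zero.** At a 16% chance rate, no responders among 12 has probability 0.84^12 = 0.12.
- **The count will feed a minimally important difference.** That remark directly follows the sentence on whether patients judged a reduction meaningful, and more naturally refers to those judgements.

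On the scale, both instruments run from 0 to 10 and the sentence also mentions distress, so the slip is small. It remains a slip, since the proportion is described as one of reduced pain.

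**Conclusion.** The point holds at low severity. With one unreplicated period per condition, the proportion of patients in whom the music was effective cannot be identified, and the observed count can overstate or understate it. This follows from the design and needs no numerical assumption.

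The share passing the cut with no effect does rest on assumptions: about 6% to 36% across the SDs, correlations, scoring and contrasts tried, with no period effect. It should be quoted only as that range, or as an example with its SD stated. The misnamed scale follows from the text alone. Nothing here touches the acceptability or feasibility objectives or the decision on a full-scale trial.

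**What to change.** Amend the Discussion sentence and any report of the count:

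1. Name one time point and contrast in advance, for example POMI versus CTL during turning, or the difference between periods in change from T0.
2. Report the proportion scoring more than 1 point lower with POMI beside the proportion scoring more than 1 point higher, and their net difference with a 95% CI. With no effect, symmetric variation and equal numbers per sequence, the two proportions are expected to be equal even if there is a period effect, so the net difference has the zero reference that the single count lacks. It remains a group-level summary and does not show who benefited.
3. Describe the first proportion as patients who *scored lower in the music period*, not as patients in whom the treatment worked.
4. Name the Faces Pain Thermometer for intensity and the NRS for distress.

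The cost is a change of wording, one extra count and one interval. No new data or design change is needed.

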### Methodological Limitations and Mitigation Strategies

The Initiative on Methods, Measurement, and Pain Assessment in Clinical Trials recommendations state that the use of a crossover trial at an earlier stage study, followed by confirmation of the results in a larger parallel-group study, is an efficient approach, as long as a washout period is carefully planned to minimize or avoid carryover effects [50]. To allow for any pain-reducing effect of the POMI to dissipate before the CTL, there will be a washout period of at least 4 hours between both intervention periods, based on previous data on the duration of the analgesic effect of music on pain [32]. Due to the sample size and to evaluate the time effect, the Friedman and Wilcoxon rank sum tests will be used when analyzing pain-related data for each subgroup [51]. To avoid response shifts due to the crossover design, baseline pain intensity will be measured for each intervention period (T_0_ in Figure 1). Because blinding will be difficult with patient participants receiving both the POMI and the CTL, there is a risk of ascertainment bias for patient participants. To address this, patient participants able to self-report will be asked about their perception of how effective they think the music is compared to the CTL. To minimize possible interruptions and noise during intervention periods, the nurse responsible for the patient will be met to discuss and plan for the best time to start the intervention period, prior to a scheduled bed turn.

Due to the current context of the pandemic and this study being conducted in an ICU setting, it is possible that limited family visits and nursing staff shortages will impact recruitment from these populations. To mitigate these possible limitations, meeting families at the bedside will be coordinated with the nursing staff.

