### Participants

#### Sample Size

A minimal sample size of 10 participants per group is recommended in pilot studies [25,26]. Because studies with repeated measures (such as crossover designs) require more time commitment from participants (ie, multiple measurements over time), an attrition rate of approximately 15% (n=2 per group) can be anticipated, which is consistent with what has been reported in previous studies conducted in the targeted population [27,28]. To account for this, the recruited sample size was estimated to be 12 participants per group.

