#### Patients

A sample size of 24 patients is targeted, with 12 being able to self-report and 12 unable to self-report. Patients able to self-report will be asked about their music preferences, levels of pain intensity, distress, and acceptability of the POMI.

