#### Preliminary Efficacy

Descriptive statistics will be computed for all outcomes (CPOT, pain intensity, and pain distress scores). The 95% CIs will be computed for each dependent variable at each time point.

Considering the small sample size for a pilot study, the potential efficacy of the POMI will be analyzed using nonparametric tests. For the dependent variables (CPOT, pain intensity, and pain distress scores), the Friedman test will be used to compare the scores at individual time points in each group separately. If the Friedman test is found to tend toward significant (*P*<.10), the Wilcoxon signed rank test will be used to compare 2 timepoints in pairs with a Bonferroni correction (.05 per number of tests) to locate the differences.

The preliminary efficacy findings will not be used to inform the decision to pursue a full-scale RCT. However, any tendency toward statistical significance (*P*<.10) or significant lower pain scores in the music period versus the control period will support that the intervention group might decrease pain over time, compared to the control group. A formal hypothesis of efficacy will need to be tested in a full-scale RCT, which will only be recommended if the POMI is deemed acceptable and feasible.

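### No POMI-versus-control effect on CPOT over all 24 patients is specified, and the undefined terms *group* and *subgroup* leave unclear whether CPOT is tested in 12 patients or 24

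*Protocol article*

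**What the plan says.** In the protocol article, Preliminary Efficacy of POMI on Acute Pain states: "For all patient participants, the CPOT will be used". Pain intensity and pain distress are added only for patients who can self-report. The Patients section gives the numbers: "A sample size of 24 patients is targeted, with 12 being able to self-report and 12 unable to self-report". Randomization to sequence is stratified by self-report status, in blocks of 4, with 3 blocks per stratum.

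Under Data Analysis, Preliminary Efficacy, the Friedman test "will be used to compare the scores at individual time points in each group separately". Pairwise Wilcoxon signed rank tests with a Bonferroni correction follow if the Friedman P value is below .10. The same section plans descriptive statistics for all outcomes and a 95% CI for each variable at each time point. It also says that lower scores in the music period than in the control period will be read as support for the intervention, and that efficacy results will not inform the decision on a full-scale RCT.

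Methodological Limitations and Mitigation Strategies describes the same analysis again: the Friedman and Wilcoxon tests "will be used when analyzing pain-related data for each subgroup". It names the rank sum test where the Methods name the signed rank test. That is a separate inconsistency, and this point does not rest on it.

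**The concern.** The secondary objective is preliminary efficacy of POMI in ICU patients, and CPOT is the only pain measure that spans both kinds of patient. In a 2×2 crossover the natural quantity is each patient's POMI score minus the same patient's control score. All 24 patients are meant to supply one. The tests as written do not target that quantity over the whole trial. They look at change over time within some unit, and that unit is not defined.

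Two things are at stake. The intended reading of music against control has no specified whole-trial contrast behind it. And if the unit is the self-report stratum, CPOT inference rests on half the patients who supply the data, so precision is given up for no saving in data collection.

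**Working it through.** **1. What *group* can mean.** The article uses the word in at least three ways.

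| Reading | Support in the article | Patients per CPOT test | POMI-minus-control effect over all 24? |
|---|---|---|---|
| Self-report stratum | Sample Size (12 per group) read with Patients (12 able, 12 unable) | 12 | No |
| Sequence | Randomization (equal allocation of both groups) | 12 | No |
| Treatment condition | Preliminary Efficacy (intervention group, control group) | 24 | No: time points are compared within one condition |

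The stratum reading is the most natural. *Subgroup* suits a set of patients better than a condition that every patient receives. Feasibility and Fidelity of Intervention also applies its 80% criterion to patients in each group, which again implies a set of patients.

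**2. The plan's own figure.** Sample Size gives: "A minimal sample size of 10 participants per group is recommended in pilot studies", then "an attrition rate of approximately 15% (n=2 per group) can be anticipated", then "the recruited sample size was estimated to be 12 participants per group".
- 10 / (1 − 0.15) = 11.76, rounded up to 12 per group; 2 × 12 = 24. The figure reproduces.
- 2 / 12 = 16.7%, consistent with roughly 15%.
- Planned completers: 12 − 2 = 10 per group, 20 in all.

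**3. Precision of a paired CPOT difference.** The 95% half-width, in units of the SD of the within-patient difference, is t(0.975, df) / √n.
- n = 12: 2.201 / √12 = 0.64
- n = 24: 2.069 / √24 = 0.42 (23 df); 2.074 / √24 = 0.42 (22 df, after fitting stratum)
- n = 10: 2.262 / √10 = 0.72
- n = 20: 2.093 / √20 = 0.47

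Ratios: 0.422 / 0.635 = 0.66 and 0.468 / 0.715 = 0.65. The interval is about one third narrower with both strata than with one. The ratio does not depend on the size of the SD, provided it is similar in the two strata.

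**4. On the CPOT scale, for illustration only.** The article gives no SD for the paired difference. For assumed SDs of 1.5, 2 and 2.5 points, the half-width goes from 0.95, 1.27 and 1.59 (n = 12) to about 0.635, 0.85 and 1.06 (n = 24, 22 df).

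Steps 3 and 4 measure the loss under the stratum reading (or the sequence reading, which also gives 12). Under the condition reading no patients are lost; what is missing is the contrast itself.

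**The case against.** The strongest reply is that the text does not confine CPOT to sets of 12. Neither analysis sentence mentions 12 or self-report status, and Preliminary Efficacy itself uses *group* for the treatment conditions. The descriptive statistics and per-time-point CIs carry no subgroup restriction. The Discussion mentions intervention comparisons and individual differences. A reader might infer that CPOT never receives any whole-trial summary; the document does not support that. These pooled summaries, however, describe scores at single time points. The strengths paragraph names no estimator or interval for the difference, and its numerical example is a 0–10 NRS. On the stratum reading, a pairwise test might set a POMI time point against a control one, but the article does not say so, and it would still use 12 patients.

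A second reply is that separate strata are informative. This stands. Self-report status drops out of a within-patient difference only as a main effect; a different treatment effect in the two strata does not. Such a difference is plausible: self-reporting patients choose headphones or pillow, state their own preferences and are not blinded, while the others get the pillow, a family member's account of their preferences, and are described as blinded. The Introduction says the effect in patients unable to self-report is unknown. So it would be wrong to infer that the stratum results have no value.

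A third reply is that an article may leave such detail to an analysis plan that is not shown. That would cover silence. Here the article names the tests, the trigger and the correction, and states the unit of analysis twice in undefined terms.

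Finally, a reader might want to express the gain as power. The article gives no CPOT effect or SD, and the planned Friedman and Bonferroni-corrected time-point tests are not a single POMI-versus-control test. Any power figure would describe assumptions rather than this plan.

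**Conclusion.** The point holds in a limited form. The unit of the CPOT analysis is undefined, and on none of the available readings is a whole-trial POMI-minus-control effect specified, although the plan means to interpret music against control. If the unit is the stratum, the 95% interval for a paired difference is about 1.5 times as wide as it could be (0.64 against 0.42 SD; 0.72 against 0.47 SD at planned completers). This rests on a t-based interval and similar SDs in the two strata. Widths in CPOT points rest on assumed SDs. The stronger claim, that CPOT is definitely analysed only in twelves, is not established. Priority is minor: efficacy is a secondary, preliminary objective and does not feed the decision on a full-scale RCT.

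**What to change.** Define *group* and *subgroup* wherever the pain analysis uses them, and use the same terms in the Methods and the Discussion. For CPOT, add the within-patient POMI-minus-control difference over all patients at a stated time point, stratified by self-report status, with a 95% CI. Report the two stratum estimates with their intervals next to it, since the effect may differ between them. Keep pain intensity and pain distress in the self-reporting patients, where they are measured. The descriptive summaries and time-point tests can remain.

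The cost is analysis wording; no new data are needed. The drawback is that the pooled figure averages over two strata whose effects may differ, which is why the stratum results should always accompany it.
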